**Study Design / Financial Support**

Study Design: Intervention/Experimental

**Health conditions or problems**

gestational hypertension

hypertensive pregnant woman

**General Descriptors for Health Conditions**

**ICD1-10: International Classification of Diseases**

O13 Gestational [pregnancy-induced] hypertension without significant proteinuria

**DeCS: Health Science Descriptors**

hipertensão gestacional hypertension, pregnancy induced hipertensiòn inducida en el embarazo hipertensão induzida pela gravidez

**Specific Descriptors for Health Conditions**

**ICD1-10: International Classification of Diseases**

O13 Gestational [pregnancy-induced] hypertension without significant proteinuria

**DeCS:Health Science Descriptors**

hipertensão gestacional hypertension, pregnancy-induced hipertensión inducida en embarazo

**Nature of Intervention**

Another integrative and complementary practice, manipulative treatment

**Intervention Descriptors**

osteopathic manipulation

**ICD list**

M90.8 Osteopathy in other diseases classified elsewhere

**DECS Description DECS**

**list of DECS**

osteopathic manipulation, osteopathic manipulation, osteopathic

**Drawing:**

cohort study

**Financial support**

Self-funded

**Key words**

integrative and complementary practices

fetal risk

osteopathy

osteopathic manipulation

**Study Details**

**Summary:**

The study seeks to evaluate the effects of osteopathic manipulative treatment (OMT) on the diaphragms in the hemodynamics of chronic and gestational hypertension in hypertensive pregnant women. OMT is already widely implemented as a therapy in normotensive pregnant women, including several RCTs proving its effectiveness in controlling musculoskeletal conditions. The search for OMT throughout pregnancy is a reality in countries like the USA and Australia. Australian observational studies (1,2) with pregnant women attest to the many women who seek and good results. In the USA, there was a reduction in complications during pregnancy and childbirth in a multicentric survey in osteopathic hospitals on pregnant women who had their prenatal care with OMT monitoring (3). Already in an ECR with a therapy-sacral skull, a specialty of osteopathy, a slight improvement in the pelvic pain of the pregnant women was observed (4). all studies do not report intercurrences or risks for pregnant women submitted to BMT throughout pregnancy. The present study, however, seeks to evaluate the possibility of improving perfusion with BMT in hypertensive pregnant women. As osteopathy is an integrative practice that does not use medication, positive research results could place it as an auxiliary therapy in controlling hypertension in hypertensive pregnant women.

The study provides a follow-up of the pregnant women who adhere to the research, from their acceptance until the end of the pregnancy. Therapy will be performed on the same days as the routine IFF prenatal consultations

References Requested

1- FRAWLEY, J. et al. Prevalence, and characteristics ofwomen who consult with osteopathic practitioners during pregnancy; a report from the Australian Longitudinal Study on Women’s Health (ALSWH).

Journal of Bodywork and Movement Therapies, v. 20, no. 1, p. 168–172, Jan. 2016.

2- SMITH, S. A study into osteopathic treatment of pregnant women in NSW and Queensland. PhD Thesis—[s.l.] Victoria University, 2005.

3-KING, H. H. et al. Osteopathic Manipulative Treatment in Prenatal Care: ARetrospective Case Control Design Study. P. 6, [n.d.].

4- ELDEN, H. et al. Effects of craniosacral therapy as adjunct to standard treatment for pelvic girl pain in pregnant women: a multicenter, single blind, randomized controlled trial. Acta obstetricia et gynecologica Scandinavica, v. 92, no. 7, p.775–782, 2013.

**Introduction**

Gestational hypertensive disorders (GHD) are a worldwide public health problem. They affect 6 to 8% of women and are the most common cause of pregnancy-related morbidity and mortality worldwide (1,2). GHD represents the main reason for fetal obituary and neonates with perinatal hypoxia (3,4). In Brazil, according to data from the 7th Brazilian guideline on arterial hypertension, the disease affects 7.5% of pregnancies and about 2% progress to eclampsia (5). The diagnosis of the hypertensive disease is given by the presence of high blood pressure. Systolic (SBP) at 140 mmHg and diastolic (DBP) at 90 mmHg, found in an average of at least two measurements in a period of 15 min (1–3). Gestational hypertensive disorders (GHD) are classified as pre-existing when the pregnant woman already presents a condition hypertensive before pregnancy; gestational hypertension (HG), when it appears during pregnancy and pre-eclampsia (PE). AS DHG usually is associated with other comorbidities such as diabetes, kidney disease, hematological disorders, liver, lung, and neurological pathology (2,3).HG manifests itself from the 20th week of gestation onwards and increases the risk of PE and eclampsia. The latter put the life of the fetus and the mother at risk as they are correlated with stroke and pulmonary edema (PE), which are the significant causes of mortality in this pathology. The HG approach involves changes in lifestyle and eating habits in addition to medication use. At the however, the use of medicines during the gestational period is complex since many of the drugs available go beyond the placental barrier and reach the bloodstream of the embryo, which, as it does not have a fully developed body system, is subject to adverse effects (6). Given this scenario, it is necessary to search for therapeutic alternatives for the treatment of DHG. In recent years, the increased demand for integrative and complementary practices (PIC) in the prevention and treatment of various diseases led the Organization World Health Organization (WHO) asks member states to formulate laws to integrate these practices into their health systems. THE Osteopathy is part of the list of PICs recognized in several countries, including Brazil. Osteopathic manual treatment (BMT) is configured as a non-invasive therapy without the use of drugs, where the professional diagnoses and treats somatic dysfunctions through the hands (6). The disorders treated by osteopathy are cataloged as diseases of the musculoskeletal system (ICD-10, M99.00-09) and identified by the TART parameters (Tenderness, Asymmetry, Range of motion change, Tissue texture change) (7). The importance of increasing research about OMT in pregnant women is due to the need to find safe and effective treatment practices during pregnancy, especially in high-risk pregnancies (8–10).

**Hypothesis:**

Osteopathic manipulative treatment alters the hemodynamics of pregnant women

**Primary Purpose:**

To evaluate the hemodynamic effects of OMT on the mean BP of pregnant women.

**Secondary Purpose:**

To compare the effects of OMT on maternal-fetal vascularization between groups of pregnant women.

Changes in quality of life of pregnant women through the SF-36 quality of life questionnaire.

Perinatal outcomes among the group of pregnant women.

**Proposed Methodology:**

This is a cohort study with a convenience sample of normotensive and hypertensive pregnant women followed at the prenatal clinic and in the IFF/Fiocruz pregnant women's ward. The prenatal service at the IFF “takes care of pregnant women with a gestational age of less than 24 weeks, without clinical comorbidities and with indications such as infectious diseases with risk of fetal repercussion, adolescents aged Fifteen years, history of previous malformation pregnancies, maternal age 35 years or older, multiple gestations, hemolytic disease perinatal, and maternal gynecological malformation. "The services will take place at the Fernandes Figueira Institute, a unit of the Oswaldo Cruz Foundation dedicated to teaching, research, and technological development. The Institute is recognized as a reference center for the health of women, children, and adolescents. It has the “MS assignment of assisting, coordinating and evaluating actions aimed at women's and children's health within the scope of national." The research will be composed of two groups: a control group formed by normotensive pregnant women and an exposed group of pregnant women hypertensive. The appointments will take place on Tuesdays and Thursdays at the prenatal outpatient clinic or the pregnant women's ward of the IFF, with all pregnant women who agree to participate in the research. These will be met with OMT from their entry into the study until the time of termination of pregnancy. OMT consultations will occur at each routine visit of these pregnant women to the outpatient clinic. Pregnant women will respond to a standard form prepared by the researchers in addition to a life questionnaire, the SF-36, applied after each meeting. The average duration of consultations takes around 30 to 40 minutes, and the techniques chosen are widely recognized by osteopathic professionals and described in articles as safe practices. There will be no maneuvers on the patient's abdomen, just as there will be no maneuvers on the viscera, as it is not a practice of visceral osteopathy. Before and after each visit, the BP of the pregnant woman will be evaluated using a blood pressure device. OMRON HEM-7320F, validated for research by the Brazilian College of Cardiology1F. BP will always be measured on the left arm, with the patient sitting and in left lateral decubitus. Pregnant women who are hospitalized in the ward, they will also be treated with the same OMT but will have a different measurement. Before the OMT observes, the data of blood pressure (BP), heart rate (HR), and respiratory rate (RR) are present in the electronic monitor (without any interference by the human operator). An ultrasound (US) will be performed for fetal evaluation through the doppler of the uterine, umbilical and cerebral arteries, and then the same life questionnaire (QoL) will be applied. Only after these measurements will OMT occur. After 30 minutes of the intervention, the blood pressure, heart rate, and respiratory rate data on the electronic monitor will be measured again (without interference from the human operator). A new ultrasound will be performed for fetal evaluation through the doppler of the uterine, umbilical and cerebral arteries. One recent evaluation will be carried out 24 hours after OMT. Blood pressure, heart rate, and respiratory data will again be observed on the electronic display (without any interference by the human operator). Another ultrasound will be performed for fetal evaluation through the doppler of the uterine, umbilical and cerebral arteries, and then the same life questionnaire will be applied. The OMT protocol includes techniques for balance ligament (BLT), myofascial, muscular energy, and cranial tensions. High-velocity and low-speed (HVBA) styles were excluded. Pregnant women in both groups will maintain standard obstetric and drug treatment and must sign a free-term consent, their willingness, and awareness of participating in the research.

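### Change in SF-36 is a stated purpose, but no SF-36 before the first OMT is stated for clinic women, while ward women are measured before OMT and 24 hours later

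*Protocol*

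**What the plan says.** The Secondary Purpose section of the protocol names this aim: "Changes in quality of life of pregnant women through the SF-36 quality of life questionnaire".

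The timing is set out under Proposed Methodology, separately for the two settings.

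- **Clinic.** On the start of treatment: "These will be met with OMT from their entry into the study until the time of termination of pregnancy". On its frequency: "OMT consultations will occur at each routine visit of these pregnant women to the outpatient clinic". On the questionnaire, women fill in a study form "in addition to a life questionnaire, the SF-36, applied after each meeting". Blood pressure is handled differently: "Before and after each visit, the BP of the pregnant woman will be evaluated using a blood pressure device".
- **Ward.** Of inpatients the protocol says that "they will also be treated with the same OMT but will have a different measurement". After the monitor readings and the Doppler examination, the order is "and then the same life questionnaire (QoL) will be applied. Only after these measurements will OMT occur". The follow-up is described as "One recent evaluation will be carried out 24 hours after OMT", and the questionnaire is repeated on that occasion. None is listed at the 30-minute re-measurement.

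**The concern.** To speak of a change in quality of life under OMT, one needs a score from before OMT. Ward women have one. For clinic women none is stated, and a baseline that was not collected cannot be recovered by any later analysis. A statistical analysis plan could not repair this, because the timing of assessments is fixed in the protocol itself.

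The design makes the gap more important. Both groups receive OMT and there is no untreated arm, so the only reference point for quality of life under OMT is each woman's own score before treatment. Without it, the clinic data cannot show what happened to quality of life when OMT began. They show only how scores moved between one treated occasion and the next.

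The two settings also yield different measures under one name, so a single figure for change in SF-36 would have no clear meaning.

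**Working it through.** The protocol gives no figure to reproduce on this point. The check sets the two schedules beside the stated purpose.

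| Step | Clinic women | Ward women |
|---|---|---|
| Before OMT | Blood pressure; no SF-36 stated | Monitor data, Doppler, questionnaire |
| OMT | At every routine visit, from study entry | Same OMT |
| Shortly after OMT | Blood pressure; SF-36 | At 30 minutes: monitor data and Doppler, no questionnaire listed |
| 24 hours after OMT | Nothing stated | Monitor data, Doppler, questionnaire |

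**Step 1: first score in the clinic.** OMT begins at entry, each routine visit is an OMT session, and the SF-36 follows the session. Write S1, S2, S3 for the scores after sessions 1, 2, 3. The first available value is S1, which already follows treatment. No earlier administration to clinic women appears anywhere in the protocol.

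**Step 2: changes that can be formed.**

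- Clinic: S2 − S1, S3 − S1 and so on, each a difference between two post-session scores.
- Ward: W24 − W0, where W0 is taken before OMT and W24 at 24 hours.

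The value that would match W0 in the clinic, S0, does not exist. So S1 − S0, the change across the first session, cannot be observed in any clinic woman.

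**Step 3: whether the two changes are the same quantity.** They differ in starting point (treated or not yet treated that day) and in interval (24 hours on the ward; between routine visits in the clinic, at a spacing the protocol does not give). They should not be combined as one measure.

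**Step 4: number of women affected.** The planned sample is 80. If a share p is treated in the clinic, 80 × p women have no pre-OMT score. The protocol does not state p. Purely as an assumption, p = 0.5 gives 80 × 0.5 = 40 women and p = 0.9 gives 80 × 0.9 = 72. These values illustrate scale and are not evidence about the trial.

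**The case against.** The strongest reply is that the protocol does not rule out an SF-36 at entry. It says when the questionnaire is applied and does not say that it is applied at no other time. The text also reads like a loose translation and uses several words for the same encounter. This stands to the extent that the point must be worded as no pre-OMT SF-36 being *stated* for clinic women. It does not remove the point: the same section pairs clinic blood pressure before and after each visit, and gives ward women a questionnaire explicitly before OMT. The SF-36 sentence could also be read as covering all women, but clinic women would still have no stated pre-OMT score.

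A second reply is that the SF-36 has low weight here. It appears in one line under Secondary Purpose, is absent from the Primary Outcome and Secondary Outcome sections, and does not touch the blood pressure aim. That is correct and limits the priority of the point.

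A reader might go further in several ways that the protocol does not support:

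- *That the comparison of hypertensive with normotensive women is confounded by setting.* It seems natural to expect more hypertensive women on the ward, but no split by group is given. The SF-36 purpose itself names no comparison between groups; that wording belongs to the vascularization purpose. The most that can be said is that such a comparison could be affected if the mix differs.
- *That clinic and ward changes will be pooled.* The protocol nowhere says so.
- *That scores taken straight after a session, or 24 hours apart, mostly reflect passing mood or a wish to please the therapist.* Nothing in the protocol supports this, and it does not say who administers the questionnaire.

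**Conclusion.** The concern holds in a limited form. The stated schedule does not deliver the stated purpose for clinic women: a change from a pre-OMT score can be formed only for ward women, and what can be formed in the clinic is a different quantity.

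This rests on two readings of Proposed Methodology: that the sentence on the SF-36 after each meeting is the clinic schedule, and that silence about an earlier questionnaire means none is planned. Both are the more likely reading. If an entry questionnaire is in fact given, the remedy is simply to say so.

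The size is all clinic women, an unknown share of 80. An effect on any comparison between the blood pressure groups is conditional on a clinic/ward imbalance that the protocol does not describe. The point deserves correction because the loss cannot be repaired afterwards, but it concerns one secondary purpose and leaves the primary purpose untouched.

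**What to change.** Amend Proposed Methodology so that every woman, in clinic or on the ward, completes the SF-36 at enrolment before her first OMT session. Keep the later administrations as they are. Analyse the later clinic scores adjusted for that baseline score, and report the ward 24-hour change separately, without pooling it with the clinic changes.

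The cost is one extra questionnaire per clinic woman and a short change of wording. No treatment is altered.

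Replacing the later questionnaires by a single one at the last visit before delivery would look tidier, but that visit cannot be recognised when it takes place. It would also discard the ward 24-hour score, which completes the only before-and-after pair now in the protocol.

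Two limits remain and should be stated in the report. Every woman receives OMT, so the change mixes OMT with advancing pregnancy and should be described as change from baseline, not as a treatment effect. The later clinic scores would also still be taken after a session, whereas the baseline would be taken before one.

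### The pre-treatment BP is not tied to the start of OMT, so the within-session change also contains the ultrasound, questionnaire or consultation

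*Protocol*

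**What the plan says.** The Primary Purpose is "To evaluate the hemodynamic effects of OMT on the mean BP of pregnant women". The timing of the BP readings is set in the Proposed Methodology, separately for the two settings.

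- **Ward.** The account starts with the monitor: "Before the OMT observes, the data of blood pressure (BP), heart rate (HR), and respiratory rate (RR) are present in the electronic monitor". Doppler of the uterine, umbilical and cerebral arteries follows, then the questionnaire, and the text adds: "Only after these measurements will OMT occur". The next BP is described thus: "After 30 minutes of the intervention, the blood pressure, heart rate, and respiratory rate data on the electronic monitor will be measured again". A later set of readings is also planned: "One recent evaluation will be carried out 24 hours after OMT".
- **Clinic.** "Before and after each visit, the BP of the pregnant woman will be evaluated using a blood pressure device". Treatment is attached to routine care: "OMT consultations will occur at each routine visit of these pregnant women to the outpatient clinic". The Summary likewise places therapy on the days of routine prenatal consultations.

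Both the normotensive control group and the hypertensive exposed group are treated from entry to the end of pregnancy. The section states no rest period before the first reading.

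**The concern.** A before-after change measures what happens between its two readings. Here the first reading is not the value at the start of OMT. On the ward, an ultrasound and a questionnaire lie between it and the treatment. In clinic, on the literal wording, a prenatal consultation may lie inside the interval as well.

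This matters because nobody goes without OMT. Comparing normotensive with hypertensive women compares two treated groups, so it cannot isolate what OMT does. The within-session change is then the only short-term contrast that speaks to the primary purpose, and the Data Analysis Methodology does plan to relate OMT to changes in hemodynamics. The Summary and the Benefits section say that a favorable result would support OMT as an aid in BP control. A change produced by the other procedures could be taken for that result, and a drift the other way could hide a real effect.

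The order of measurements is data collection. A reading that was never taken cannot be recovered by any later analysis plan.

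**Working it through.** The protocol gives no figure to reproduce on this point. The check has two parts.

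**1. What lies between the two readings**

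| Setting | First BP | Between first BP and OMT | Second BP |
|---|---|---|---|
| Ward | Monitor reading, described first | Three-artery Doppler, questionnaire; no repeat BP | 30 minutes after OMT, then at 24 hours |
| Clinic | Before the visit | Whatever part of the visit precedes OMT | After the visit |

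The ward change is therefore ultrasound + questionnaire + OMT session + 30-minute wait. The clinic change, read literally, is consultation + OMT session. Consultations are said to last 30 to 40 minutes on average. No pair of readings in either setting covers an interval without OMT, so the non-OMT part cannot be estimated from the planned data.

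**2. How much drift would be needed to mislead (illustration only)**

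Inputs:
- Total sample size 80, from the protocol. The split between groups is not given; n = 40 per group is assumed.
- SD of the within-session change: assumed 8, 10 or 12 mmHg.
- Drift unrelated to OMT: assumed 3 mmHg, with 2 and 5 mmHg for range.
- True OMT effect: set to zero. Two-sided paired t-test at 5%.

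The non-centrality is λ = drift / (SD / √n). The rejection probability is P(|T| > t₀.₉₇₅,ₙ₋₁), where T is non-central t with n − 1 degrees of freedom and non-centrality λ. For n = 40 the critical value is 2.02.

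For a 3 mmHg drift:
- SD 8: SE = 8/√40 = 1.265, λ = 2.37, probability 64%
- SD 10: SE = 10/√40 = 1.581, λ = 1.90, probability 46%
- SD 12: SE = 12/√40 = 1.897, λ = 1.58, probability 34%

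Across the same SDs, a 2 mmHg drift gives 34% down to 18%, and a 5 mmHg drift 97% down to 73%. If all 80 women are pooled, 3 mmHg gives 91%, 76% and 60%. With no drift the rate is the nominal 5%.

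**The case against.** Several points on the other side have force.

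- **Visit may mean only the OMT consultation.** The neighboring sentences speak of OMT consultations, and the text reads as a translation. If so, the clinic readings already bracket OMT. This stands as a possible reading; it does not touch the ward, and the ambiguity needs resolving anyway. In clinic the SF-36 is applied after each meeting, so it cannot be assumed to fall between the two readings.
- **The ward order is partly inferred.** That BP precedes the ultrasound comes from the order of the sentences. What is firm is that no BP is tied to the moment OMT starts.
- **The 24-hour ward reading is less exposed to short-term drift.** True, but it exists only for ward patients, shares the same early baseline and has no untreated comparison.
- **The primary outcome is the evolution of hemodynamic parameters over the third trimester.** The protocol does not name the within-session change as its primary contrast, and a drift that recurred equally at each visit would not create a trend across visits. This stands. It limits the point to the short-term contrast.

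A reader might infer more: that BP will fall through rest and settling, that regression to the mean adds to the fall, and that both will be larger in hypertensive women. The documents do not support this. They give no size or direction for any drift. Ward patients are already hospitalized and read from a monitor without operator involvement. The Inclusion Criteria set no BP threshold on the day of the session, so regression to the mean is not built into the average change.

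**Conclusion.** The concern holds in a limited form. As sequenced, the within-session BP change cannot be separated from the ultrasound and questionnaire on the ward, or, on the literal wording, from the rest of the visit in clinic. Since all women are treated, no other short-term contrast fills the gap.

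The size is unknown. The 34% to 64% range shows only that a modest drift would be enough to mislead; it rests on the assumed 3 mmHg, the assumed SDs and 40 women per group. It is not a prediction that such a drift will occur, or that it will be a fall. The underlying limitation, the lack of any untreated period or group, is larger than the timing of one reading and remains after the fix below.

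**What to change.** Keep the existing first reading (R1). Add one automated reading immediately before OMT starts (R2), on the ward after the ultrasound and questionnaire, and in clinic after any consultation. State that the clinic readings are tied to the start and end of OMT, not to the visit. Use R2 as the baseline for the within-session change.

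Report R1 to R2 descriptively, as the drift seen without OMT. Do not subtract it, scaled for elapsed time, in the primary estimate:
- **Bias.** Scaling assumes that drift is linear. Suppose BP falls 3 mmHg from R1 to R2 and 1 mmHg over the next interval, which is twice as long. An inert session would then give −1 − 2 × (−3) = +5 mmHg, a spurious rise.
- **Noise.** With independent reading errors of variance s², post minus R2 has variance 2s². The scaled difference, with scaling factor k, has [1 + (1 + k)² + k²]s², which is 6s² at k = 1 and 14s² at k = 2, or 3 to 7 times as much.

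Add a sentence saying that rest during OMT, and on the ward in the 30 minutes after it, remains inside the change, so without an untreated period or group it must not be interpreted as an effect of OMT alone.

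The cost is one or two minutes per session with equipment already in use.
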